### Location and setting

All assessments will be conducted in the Gait Laboratory within the Institute of Health and Biomedical Innovation at Queensland University of Technology, Brisbane, Australia.

### Participants

Men and women with a diagnosis of MS will be identified through a pool of sampling frames including MS Queensland, local MS health care providers and community organisations across the Brisbane, Gold Coast and Logan regions, Australia. Participants will be recruited through mainstream media advertisements and written materials distributed to individuals listed on the MS Queensland database and those attending local MS clinics. Recruitment procedures will be centrally coordinated by clinical staff working within each organisation to maintain patient confidentiality. Participants will be invited to voluntarily contact the Principal Investigator for further information.

Participants will be eligible to take part if they meet the following criteria: aged over 18 years; clinical diagnosis of MS; ambulant over 100 metres with or without the use of an assistive device; and Disease Step rating of 1–4 [29]. Participants rated as Disease Step 1 (mild disability: mild symptoms and/or signs) to 4 (late cane: unable to walk 25 feet without a cane/unilateral support) will be eligible to take part in this study, assuming they have sufficient ambulatory capacity to complete the gait trials.

Exclusion criteria are neurological conditions other than MS; peripheral neuropathy; currently being prescribed over-the-counter or custom-made foot orthoses; cardiovascular or orthopaedic conditions including recent injury to the back or legs limiting ambulation; unstable psychiatric condition or cognitive impairment (Short Form Mini-Mental State Examination score <24) [30]. Furthermore, enrolled participants who report an exacerbation of MS symptoms persisting >24 h, 4 weeks prior to, or at any time during, the intervention period will also be excluded from the study. All participants will initially be screened via telephone interview and invited to attend a clinical examination to confirm eligibility. Written informed consent will be obtained from all participants. This study was approved by the Medical Research Ethics Committee at The University of Queensland (#2014000781) and University Human Research Ethics Committee at Queensland University of Technology (#1500000615).

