**Methods:**

A prospective randomised controlled trial with two parallel groups will be conducted aiming to recruit 176 people with multiple sclerosis living in the community (Brisbane, Australia). Adults with a clinical diagnosis of multiple sclerosis, Disease Steps score 1–4, who are ambulant over 100 m and who meet specific inclusion criteria will be recruited. Participants will be randomised to a smooth control insole (n = 88) or textured insole (n = 88) group. The allocated insole will be worn for 12-weeks within participants’ own footwear, with self-report wear diaries and falls calendars being completed over this period. Blinded assessors will conduct two baseline assessments and one post-intervention assessment. Gait tasks will be completed barefoot, wearing standardised footwear only, and wearing standardised footwear with smooth and textured insoles. The primary outcome measure will be mediolateral base of support when walking over even and uneven surfaces. Secondary measures include spatiotemporal gait parameters (stride length, stride time variability, double-limb support time, velocity), gait kinematics (hip, knee, and ankle joint angles, toe clearance, trunk inclination, arm swing, mediolateral pelvis/head displacement), foot sensation (light touch-pressure, vibration, two-point discrimination) and proprioception (ankle joint position sense). Group allocation will be concealed and all analyses will be based on an intention-to-treat principle.

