### Randomisation and blinding

The concealed randomisation schedule will be established using a computer-generated random number sequence, and maintained by an offsite investigator who is neither involved with the enrolment nor with assessment of participants. Consecutively numbered, randomly ordered, opaque envelopes containing group allocation (in a 1:1 ratio), will be opened consecutively after baseline assessment 2, by a second research assistant who is only responsible for administering the insoles. All investigators and the first research assistant, who are involved in the enrolment or assessment of participants over the duration of the trial, will remain blinded to group allocation. Following baseline assessment 2, the Principal Investigator and first research assistant will leave the gait laboratory to ensure blinding to the insole condition. The second research assistant will then fit the participant with their allocated insole, and provide advice regarding the frequency of wear, completion of insole wear diaries, and emergency contact details for local podiatry care. Participants will be instructed not to divulge their group allocation. As it is not possible for participants to be blinded to their allocated group (those in the intervention group will be able to perceive the textured material against the sole of their foot), the full aims of the study will be concealed. Participants will not be told that the intervention is designed to provide enhanced plantar sensory information which could potentially lead to changes in gait. Such knowledge could influence how participants walk and they could purposefully alter their walking patterns between conditions; debriefing will occur upon completion of the study. Furthermore, coding of participants will not refer to group.

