### Data analysis

All analyses will be conducted in a blinded manner, on an intention-to-treat basis, with the alpha set to 0.05. We will explore frequency distributions, percentages and calculate means and standard deviations for the outcome measures. Differences between intervention and control groups in spatiotemporal gait variables, gait kinematics, foot sensation or proprioception, over the intervention period, will be explored using General Linear Models (repeated measures analysis of variance, ANCOVA), in a two group (smooth control insole; textured insole) by three phase (baseline assessment 1, baseline assessment 2, post-intervention) model. We will adjust for potential confounding variables (e.g. age, sex, disease duration) by using these as covariates. Non-parametric tests will be used where data is not normally distributed or violates the assumption of sphericity. Multiple regression modelling will be used to determine any relationships between foot sensation, proprioception and measures of gait performance. Data will be analysed using SPSS version 22 (SPSS Inc., Chicago, IL 60606, USA).

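### Excluding participants for an MS exacerbation during the intervention is a post-randomisation exclusion and conflicts with the stated intention-to-treat analysis

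*Protocol article*

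**What the plan says.** Four parts of the protocol article bear on the point.

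- **Participants (exclusion criteria).** The rule applies to "enrolled participants who report an exacerbation of MS symptoms persisting >24 h, 4 weeks prior to, or at any time during, the intervention period". Its stated consequence is that someone who reports one "at any time during, the intervention period will also be excluded from the study"; this is not merely a change in insole use.
- **Randomisation and blinding.** The allocation envelopes "will be opened consecutively after baseline assessment 2, by a second research assistant", who then fits the insole. The same section accepts that "it is not possible for participants to be blinded to their allocated group". It adds that the full aims are withheld from participants and that those who enrol and assess them stay blinded.
- **Data analysis.** "All analyses will be conducted in a blinded manner, on an intention-to-treat basis, with the alpha set to 0.05". The Abstract repeats that "all analyses will be based on an intention-to-treat principle".
- **Sample size.** 76 per group are required and 88 per group (176 in total) are to be recruited, with 15% attrition allowed over 16 weeks. The section does not say whether the 15% includes participants excluded for an exacerbation.

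The primary aim, at the end of the Background, is change in mediolateral base of support from baseline assessment 2 to the post-intervention assessment.

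**The concern.** Intention to treat keeps every randomised participant in the comparison, in the allocated group, whatever happens afterwards. A rule that takes people out because of something reported during the intervention does the opposite. A participant who reports an exacerbation in, say, week 8 is excluded under one section and analysed as allocated under another, and no sentence in the article reconciles the two.

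Three features make this more than a wording problem:

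- **The event is probably related to the outcome.** The Baseline assessments section itself links acute relapse to changes in walking impairment, so the rule tends to remove people whose gait has worsened.
- **The trigger is the participant's own report.** No blinded confirmation is described and participants know which insole they wear, so the rate of exclusion could differ between arms.
- **The loss cannot be undone.** If the week-16 gait measurement is not taken, no later analysis can restore it.

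**Working it through.** **1. Timeline.** Baseline 1 is at week 0 and baseline 2 at week 4. The envelope is then opened and the insole fitted. Twelve weeks of wear follow, with the final assessment at week 16. The exclusion rule has two halves:

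- The 4 weeks before the intervention fall before allocation. Exclusion there is an eligibility matter and does not conflict with intention to treat.
- The intervention period lies wholly after allocation. Exclusion there is post-randomisation.

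**2. Two readings of exclusion.**

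- Removal from the analysis set: this contradicts intention to treat directly.
- Withdrawal from follow-up, with the participant nominally kept in the allocated group: baseline values exist but the week-16 value does not, and the primary aim is the change between them.

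Under both readings the observed comparison is made in a subset defined after randomisation. Nothing in the article says that excluded participants are still assessed at week 16.

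**3. The plan's own sample size.** Inputs from the Sample size section: SD 5.11 cm, change 1.66 cm, power 80%, alpha 0.05 (taken as two-sided). The paired formula gives n = ((1.960 + 0.842) × 5.11 / 1.66)² = 74.4, so 75. The paired t version gives 76.3. The stated 76 is reproduced closely. For attrition, 76 × 1.15 = 87.4, so 88, as stated. The number expected at week 16 is 88 × 0.85 = 74.8 per group.

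**4. Numbers affected.** No exacerbation rate is given. For an assumed 5% to 15% over 12 weeks: 176 × 0.05 = 8.8 and 176 × 0.15 = 26.4, so about 9 to 26 participants.

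**5. Power if none of these losses lies within the 15%.** Number per group = 88 × 0.85 × (1 − e). Power on the protocol's paired calculation = Φ(1.66 × √n / 5.11 − 1.960).

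| Assumed excluded, e | n per group | Power |
|---|---|---|
| 0% | 74.8 | 80.2% |
| 5% | 71.1 | 78.2% |
| 10% | 67.3 | 76.0% |
| 15% | 63.6 | 73.6% |

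If the 15% already covers every such loss, the top row applies and nothing further is lost. The paired calculation is used only because it is the protocol's own. Whether it suits a comparison of two independent groups is a separate question.

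**6. Bias.** Let participants with an exacerbation worsen by w cm after baseline 2, and let the excluded proportions be r(textured) and r(smooth). Exclusion then shifts the between-group difference in change by about (r(textured) − r(smooth)) × w.

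- Equal rates and equal w: shift = 0.
- Assumed 15% against 5%, w = 1 cm: 0.10 × 1 = 0.1 cm.
- The same rates, w = 3 cm: 0.10 × 3 = 0.3 cm.

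Against the planning effect of 1.66 cm this is 6% to 18% (0.1/1.66 and 0.3/1.66). The sign depends on which arm loses more. All rates and values of w here are assumptions.

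**The case against.** The strongest reply is that the rule sits in an eligibility paragraph and speaks of the study, not of the analysis set. It may mean withdrawal, with definitions of the analysis population and the handling of missing data left to a fuller document. That reading is open, and it turns deletion into a missing-outcome problem. It does not remove the conflict: the protocol itself would be causing the primary outcome to go uncollected because of a post-randomisation event.

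Several stronger inferences are tempting, and the article does not support them.

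- **That reporting will differ by arm.** Nothing shows this. The study aims are concealed, the control is also an insole, and assessors are blinded. Concealment of the aims lessens the risk but does not remove it. Blinded assessment does not help here, because the selection happens before the outcome is measured.
- **That the exclusions come on top of the 15%.** The Sample size section does not say so. Its benchmarks are overall retention rates (82%, 88%, 90%) in other 12-week MS trials, which may include relapses.
- **That the rule accounts for the whole gap between 67 and 76.** The expected number is already 74.8 without any exclusion. The increment at an assumed 10% is about 7.5 per group (74.8 − 67.3).
- **That the subset is post hoc.** It is prespecified. The difficulty is that membership is decided after randomisation.
- **That a wider base among relapsing participants is itself the bias.** A difference already present at baseline 2 cancels in a change score. Only worsening after baseline 2 counts.

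**Conclusion.** The point holds as a contradiction within the protocol. Exclusion for an exacerbation during the intervention is post-randomisation and cannot be squared with an intention-to-treat analysis of all outcomes. This rests on the text and the timeline alone and needs no assumed figure. The half of the rule covering the 4 weeks before the intervention is not at fault.

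The consequences are uncertain in size. At assumed rates of 5-15%, 9 to 26 of 176 participants are affected. The cost in power ranges from nothing, if the 15% allowance already covers them, to about 4 percentage points (80.2% to 76.0%) at an assumed 10% on top. The bias ranges from zero to about 0.3 cm under the assumptions shown. The size is modest, but the conflict decides who contributes to the primary comparison, and it has to be settled before data go uncollected.

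**What to change.** Reconcile the exclusion criteria with the intention-to-treat statements in the Abstract and Data analysis:

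- Limit the exclusion to exacerbations reported before randomisation, that is, in the 4 weeks between the two baseline assessments.
- After randomisation, keep every participant in follow-up, invite them to the post-intervention assessment, and analyse them in their allocated group.
- Record each exacerbation as an event, by arm.
- Report the analysis without participants who had an exacerbation as a sensitivity analysis only.

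The cost is a short amendment and somewhat more outcome variance. Recovery of the data will also be incomplete. The gait session has five trials on each of two surfaces in four footwear conditions, and fatigue already limited completion for some pilot participants, so some people in an exacerbation may be unable to finish it. Insole wear and care during an exacerbation are clinical matters and are not addressed here.

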### Randomisation and blinding

The concealed randomisation schedule will be established using a computer-generated random number sequence, and maintained by an offsite investigator who is neither involved with the enrolment nor with assessment of participants. Consecutively numbered, randomly ordered, opaque envelopes containing group allocation (in a 1:1 ratio), will be opened consecutively after baseline assessment 2, by a second research assistant who is only responsible for administering the insoles. All investigators and the first research assistant, who are involved in the enrolment or assessment of participants over the duration of the trial, will remain blinded to group allocation. Following baseline assessment 2, the Principal Investigator and first research assistant will leave the gait laboratory to ensure blinding to the insole condition. The second research assistant will then fit the participant with their allocated insole, and provide advice regarding the frequency of wear, completion of insole wear diaries, and emergency contact details for local podiatry care. Participants will be instructed not to divulge their group allocation. As it is not possible for participants to be blinded to their allocated group (those in the intervention group will be able to perceive the textured material against the sole of their foot), the full aims of the study will be concealed. Participants will not be told that the intervention is designed to provide enhanced plantar sensory information which could potentially lead to changes in gait. Such knowledge could influence how participants walk and they could purposefully alter their walking patterns between conditions; debriefing will occur upon completion of the study. Furthermore, coding of participants will not refer to group.

### Intervention

In this randomised controlled trial we will investigate two different shoe insoles: textured insoles and smooth (control) insoles. Both insoles have been implemented in previous research strategies in pwMS [20], older fallers [23] and middle-aged adults [31]. The textured insole (Evalite Pyramid ethyl vinyl acetate (EVA), 3 mm thickness, shore value A50, black, OG1549; Algeos PTY Ltd., Liverpool, UK) was selected from a range of EVA soling materials, and has small, pyramidal peaks with centre-to-centre distances of approximately 2.5 mm. The smooth control insole (Medium Density EVA, 3 mm thickness, shore value A50, black, OG1304; Algeos PTY Ltd., Liverpool, UK) was chosen from a range of plain EVA materials and has a flat surface with no indentations. Insoles will be tailored to each participant’s shoe size. An experienced podiatrist will oversee and advise on the delivery of insoles, and any podiatry-related issues including insole fit, durability and dermatological or peripheral changes at the foot during the intervention period. Participants will be instructed to wear their allocated insoles, in their own shoes, as much as possible. All assessments of balance and gait will be conducted with the participants wearing standardised footwear (Donated by Pacific Brands Australia Pty Ltd), comprising a basic construct rubber-soled shankless shoe with a soft canvas upper [32], into which the insoles will be inserted. This standardisation will control for any possible insole/shoe interactions across participants, which could impact the findings. To allow for familiarisation to the footwear, participants will be instructed to walk for 5 minutes in the standardised shoes prior to testing.

### Primary outcome measures

#### Spatiotemporal gait variables

The primary gait measure will be ML base of support when walking over an even and uneven surface. Our pilot study demonstrated that after 2-weeks wear of the textured insoles, the significant mean reduction in base of support was 1.7 cm (*P* = 0.02) compared to baseline measures [20]. The magnitude of this effect is highly clinically relevant as previous research indicates a mean difference of ~2 cm in base of support exists between pwMS and healthy controls [6, 7]. This suggests that the textured effect is clinically significant, and may be of sufficient magnitude to reduce base of support to a level similar to healthy adults.

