This randomised controlled trial will determine whether wearing textured shoe insoles for 12-weeks can improve gait when walking over even and uneven surfaces in pwMS. The primary aim of this study is to explore whether prolonged wear of textured insoles alters ML base of support (as a measure of walking stability) from baseline assessment 2 to the post-intervention assessment. Secondary aims are to explore whether prolonged wear of textured insoles alters other spatiotemporal gait parameters including stride length, stride time variability, double-limb support time and gait velocity, gait kinematics (specifically lower limb joint and trunk movement), and changes in the perception of foot sensation or proprioception, as underlying mechanisms associated with improvements in spatiotemporal gait parameters.

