### Sample size

Sample size has been calculated for the primary outcome measure, ML base of support during even surface walking, based on our pilot data [20]. Our preliminary study reported mean (SD) readings at baseline for base of support of 13.78 (5.11) cm and a significant mean change of –1.66 cm (*P* = 0.02) at 2-weeks post intervention. With a power of 80 %, and alpha level of 0.05, a calculation for two related groups indicated that 76 participants were required in each group. In our pilot study, we recruited 46 pwMS, with no loss to follow-up across two visits (although completion of all test procedures was limited by fatigue in some participants). As this randomised controlled trial involves a longer intervention period, we will allow for a 15 % attrition rate. An 85 % retention rate over a 16-week period (baseline assessments at week 0 and week 4, intervention 12-weeks, post-intervention assessment at week 16) is appropriate based on previous MS intervention studies. Three randomised controlled trials with 12-week intervention periods conducted in pwMS, report retention rates of 82 % [27], 88 % [11], and 90 % [28]. Therefore, 88 participants per group will be recruited, giving a total of 176 participants.

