### Gait

Gait performance will be evaluated by completing a 12 m walk over an even surface and an uneven surface. The even surface will consist of a level, vinyl material: the top cover of an instrumented walkway (GAITRite^®^, CIR Systems, Inc., Havertown, PA 19083, USA). The GAITRite^®^ system is an electronic walkway, approximately 8.2 m long (the active area being 0.61 m wide and 7.32 m long), which has been shown to have high reliability [48, 49]. The uneven surface (placed directly on the laboratory floor, adjacent to the GAITRite^®^ walkway) will consist of two layers of thick soft foam, over which small blocks of wood of uneven shapes and sizes will be spread in a random manner, with a top layer of artificial grass covering the walkway, using previously described methods [50]. Maintenance of stability when walking requires individuals to control their centre of mass within a constantly changing base of support; this becomes even more challenging when the surface is uneven, increasing the risk of loss of balance, resulting in a fall. Deficits in balance control during walking or, conversely, the therapeutic benefit of interventions (such as shoe insoles) on walking performance may only become apparent when the balance challenge is sufficiently demanding. The uneven walking surface will emulate a situation encountered in daily life. A start and finish line will be marked on the floor 2 m in front and 2 m behind both the even and uneven surface walkways, allowing participants to accelerate and decelerate outside the walkways [48]. Participants will be positioned at the start line and instructed to walk at their comfortable, self-selected walking pace. Five walking trials will be completed on the even surface and five trials on the uneven surface, each whilst barefoot, wearing standardised footwear only, and wearing two different shoe insoles (textured and smooth) within standardised footwear. The test sequence (footwear condition, surface) will be randomised. Spatiotemporal gait variables will be measured using the GAITRite^®^ system (sampling rate 80 Hz) when walking over the even surface, and using an 11-camera Vicon^®^ motion capture system (Vicon, 6 × MX13 and 5 × T40 cameras, giganet control box, with a MX Net and Mx Link), sampled at 200 Hz, when walking over the uneven surface. Participants will have multiple reflective markers attached to their body, following the Vicon PlugIn Gait full body model. The Vicon system records the position of reflective markers placed at standardised anatomical sites on the upper and lower body and will be used to measure spatiotemporal gait variables and gait kinematics.

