### Post-intervention assessment

Gait, foot sensation and proprioception will be assessed within 2 weeks of the end of the 12-week intervention period, using the same procedures employed at baseline. A 12-week intervention period will provide maximal time to allow for the accrual of any sensory training effects and accumulation of meaningful changes in outcome measures, in particular for participants with MS who show minimal gait disturbance at baseline and currently engage in an active lifestyle. This intervention period is consistent with previous randomised controlled trial intervention studies conducted in pwMS [11, 27, 28], and footwear intervention trials [55, 56]. This final point of assessment will (1) quantify whether any immediate changes in gait, observed at baseline, have accrued over time, or if additional effects can be seen and (2) determine whether there are any alterations in the perception of foot sensation or proprioception, which may suggest the insoles have a sensory training effect. Participants will be asked to return their insole wear diaries and falls calendars at this time. Participants will also be asked to rate the level of comfort experienced when wearing the insoles by way of a series of 100 mm visual analogue scales used in previously published research [57].

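### The primary outcome is even and uneven walking in one place and even walking alone in another, with no success rule and no footwear condition named, so the stated alpha and power do not describe it

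*Protocol article*

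**What the plan says.** Two places make both surfaces primary. The Abstract (Methods) states "The primary outcome measure will be mediolateral base of support when walking over even and uneven surfaces", and the Primary outcome measures section states "The primary gait measure will be ML base of support when walking over an even and uneven surface".

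The Sample size section differs: "Sample size has been calculated for the primary outcome measure, ML base of support during even surface walking".

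The primary aim, at the end of the Background, fixes the time contrast but no footwear condition. It asks whether prolonged wear "alters ML base of support (as a measure of walking stability) from baseline assessment 2 to the post-intervention assessment".

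The Gait section has participants walk on both surfaces "each whilst barefoot, wearing standardised footwear only, and wearing two different shoe insoles (textured and smooth) within standardised footwear". The post-intervention visit repeats this, "using the same procedures employed at baseline".

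The Data analysis section describes one model, two groups by three phases, "with the alpha set to 0.05". It includes neither surface nor footwear condition.

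**The concern.** The two descriptions of the primary outcome cannot both stand. One is a single measure on one surface. The other is a pair of measures, and a pair needs a rule: either one is enough, or both must succeed, or they are combined. The document gives no such rule.

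A second choice sits beneath the first. Base of support is recorded in four footwear conditions on each surface, and nothing says which one carries the primary comparison. Because the model has no surface or footwear term, it does not settle either question.

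The trial's main conclusion is at stake. Until surface, rule and footwear condition are fixed, the primary result can be chosen after the data are seen, and neither the 5% alpha nor the 80% power is the trial's actual figure.

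**Working it through.** **Inputs.** From Sample size: SD 5.11 cm, mean change 1.66 cm, power 80%, alpha 0.05 (taken as two-sided), 76 per group, 15% attrition, 88 per group recruited. From Primary outcome measures: 2 surfaces. From Gait: 4 footwear conditions. The correlations between tests are assumptions, since the document gives none.

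**1. The plan's own figure.** The related-groups formula is n = ((z₀.₉₇₅ + z₀.₈₀) × SD / Δ)². This gives ((1.960 + 0.842) × 5.11 / 1.66)² = 74.4, so 75. The exact paired t calculation gives 77, and 76 has 79.8% power. The stated 76 is therefore reproduced. For attrition, 76 × 1.15 = 87.4, so 88, as stated. The figure belongs to one test, on one surface, at the full 0.05. No part of it allows for a second surface.

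**2. If success on either surface suffices.** For two independent tests at 0.05, the chance of at least one false positive is 1 − 0.95² = 9.75%. By simulation of equally correlated normal statistics:

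| Assumed correlation | Two tests |
|---|---|
| 0 | 9.75% |
| 0.5 | 9.1% |
| 0.8 | 7.8% |
| 0.9 | 7.0% |

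Restoring 5% by splitting alpha (0.025 each) raises the plan's own paired calculation from 76 to 93 per group. After attrition that is 93 / 0.85 = 109.4, so 110. With 76 per group, power would be 71%.

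**3. If both surfaces must succeed.** Type I error is then at most 5%, and the cost falls on power. If each test has 80% power, joint power is 0.80 × 0.80 = 64% when independent, 73% at correlation 0.8 and 75% at correlation 0.9.

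**4. If footwear conditions are also tested separately.** Two surfaces by four conditions gives up to 2 × 4 = 8 cells. With any-success at 0.05 each, the false-positive risk is 11.9% at correlation 0.9 and 15.7% at 0.8. The ceiling, for independent tests, is 1 − 0.95⁸ = 33.7%.

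**5. If one surface and one condition are named.** Alpha stays at 0.05, and the stated 76 is unchanged on this point.

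**The case against.** The strongest reply is that the analysis plan is not shown, and that test ordering and multiplicity handling are normally left to it. That is fair for multiplicity alone, and the absence of an adjustment is not the finding. It does not cover a primary outcome that the same article defines in two different ways, one of them used to size the trial.

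Three stronger readings are tempting, and the document does not support them.

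- *Eight primary tests are planned.* The Gait section lists measurement conditions, not hypotheses. Eight is a count of cells. The model could equally be applied to one chosen condition or extended with within-person factors.
- *The type I error is 34%.* That needs eight independent tests and an any-success rule. These are walks by the same people at the same visit, so the tests are correlated, and no rule is stated. If both surfaces are required, error is not inflated at all.
- *A positive result might only reflect the immediate feel of texture, if each arm is compared in its own insole.* Both baseline assessments precede allocation and already include walking in each insole. For change from baseline assessment 2, the textured group has texture underfoot at both time points, so a constant immediate effect cancels. It would enter only if a baseline in one condition were compared with a follow-up in another, or if baseline were ignored. The protocol proposes neither.

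One further objection stands in part. Putting the even surface first sits awkwardly with the Gait section's own argument that benefit may show only when the balance task is demanding enough. The sponsor could defend the opposite order.

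**Conclusion.** The point holds as an internal contradiction with an undefined decision rule. The Abstract and the Primary outcome measures section name two surfaces, while the Sample size section names one. No section supplies a success rule or a footwear condition.

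The consequence depends on the reading. If either surface suffices, the false-positive risk is about 8–10% (correlation 0.8 to independence). It is about 12–16% if all eight cells are tested separately at correlation 0.9 to 0.8, with 34% only as an outer limit. If both are required, joint power is about 64–75% rather than 80%.

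These figures rest on assumed correlations, two-sided tests and, for joint power, 80% power on each surface taken at face value. What is established is that the error rate and power of the primary analysis are not fixed. It is not established that the trial will run at any particular inflated rate.

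**What to change.** Before group data are examined, and by dated amendment:

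1. Name one primary endpoint: change from baseline assessment 2 to the post-intervention assessment in mediolateral base of support on the even surface, which agrees with the Sample size section. Use one pre-named footwear condition that is the same in both arms and at both visits, for example standardised footwear only. Test it at 0.05.
2. Test the uneven surface in the same condition second, at the full 0.05, only if the first test is significant.
3. Make the remaining footwear conditions secondary.
4. Align the Abstract, the Primary outcome measures section and the Sample size section with this. Also reconcile the Intervention section, which places all gait assessments in standardised footwear, with the Gait section, which includes barefoot walking.

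This needs no extra participants on this point. Because the trial is registered, ethically approved and ongoing, it is an amendment and not just an edit. The real cost is that no confirmatory uneven-surface claim is possible if the even-surface test fails. Under the assumptions above, the chance of establishing both is the same 64–75%. If the sponsor prefers the uneven surface first, the order can be reversed, but the sample size must then be restated for that surface.
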